### Economic evaluation

Cost data comparisons between the groups will be made using a bootstrap regression model (using 10,000 repetitions). Either bias-corrected or percentile 95% confidence intervals will be reported depending on the level of bias in the data. Cost-effectiveness and cost-utility will be established by combining the cost data (NHS/PSS and then all services) with change scores on the PANSS and QALYs respectively. In addition, cost-effectiveness acceptability curves (CEACs) will show the probability that BPT or Pilates is cost-effective for different values placed on unit-changes in outcome. The net benefit approach will be used (i.e. the monetary value of outcome change minus the service cost) and net benefit will then be used in bootstrapped regression models. The proportion of coefficients for each resample that are above zero will indicate the probability that BPT is the most cost-effective option. The values used for the CEAC based on QALY gains will be £0 to £100,000 in £5,000 increments, which includes the threshold of £20,000 to £30,000 used by NICE. We will also report values for PANSS improvements that are linked to BPT/Pilates having a 50%, 75% and 95% likelihood of being cost-effective.

Because this project uses an active control we are essentially looking at the cost-effectiveness of receiving BPT rather than Pilates. Both BPT and Pilates are delivered by a therapist/instructor and in groups so we will be costing both interventions. However, in routine practice BPT is likely to be considered as an additional service rather than as an alternative to other active therapies. In sensitivity analyses we will therefore apply lower unit costs (25%, 50%, 75% and 100% lower) for the active control in an attempt to replicate routine practice where no or limited physical activities are provided. In case BPT could be delivered by other professionals who are more or less expensive, we will also increase/decrease the unit cost of BPT by 25% and 50% in sensitivity analyses.

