### Statistical analysis

The primary analysis will be an available case analysis following intention to treat principles. We will use mixed effect models as appropriate to the outcome, with fixed effects for the intervention, baseline level of outcome and centre, and random effects for therapy groups. For continuous outcomes we will use Stata’s *xtmixed* command, *xtmepoisson* for count outcomes, and *gllamm* for ordinal outcomes. We will assess whether there is a clustering effect due to therapist or instructor (some therapists or instructors will lead two groups), but will not take this element of clustering into account in the analysis.

We will use sensitivity analyses to explore the impact of any missing data, including extreme scenario sensitivity analyses, for example that those who are lost to follow up would have no improvement as result of any intervention. If there are sufficient missing values to warrant its use, we will use multiple imputation following an exploration of patterns of missingness. We expect to use the MAR (missing at random) assumption in this imputation. In case group dropout (as opposed to study dropout) is higher in one condition compared to the other, we will conduct a simple complier-average causal analysis with compliers defined by the active intervention. Compliance will be defined as attendance of five or more sessions of BPT.

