### Proposed sample size

A 20% reduction in the PANSS negative scale has been defined as clinically significant [25], which we would anticipate to be a difference of approximately 3 points given the eligibility criteria. To detect a difference of 3 points, with a standard deviation of 5, at alpha = 5%, and a power of 90%, 58 patients are required in each arm. Assuming an intra-cluster correlation coefficient for treatment group of 0.1, and 7 patients per group with analysable data at the end of treatment gives an inflation factor of 1.6 [24] leading to a required sample size of 93 in each arm. At six months we expect a loss to follow-up of 31%, resulting in 5.5 individuals per group on average and an inflation factor of 1.45; recruiting 128 per arm (16 groups of 8 in each arm) leaves 88 per arm at 6 months and 91% power to detect a difference of 3 points at this time point (see Figure 1). One hundred and twenty eight patients per arm, i.e. 16 groups of approximately 8 patients in each arm will give 94% power for the end of treatment analysis. We do not expect to recruit and allocate exactly eight individuals within each group but the variation in group size will be small and will not materially affect the power of the trial.

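### The bootstrap regressions for costs and net benefit carry no therapy-group element; if patients are resampled singly and the ICC is positive, economic uncertainty will be understated

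*Protocol article*

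**What the plan says.** All references are to the protocol article.

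- **Economic evaluation, costs:** "Cost data comparisons between the groups will be made using a bootstrap regression model (using 10,000 repetitions". Bias-corrected or percentile 95% intervals follow.
- **Economic evaluation, net benefit:** "net benefit will then be used in bootstrapped regression models". The CEAC is read from these fits: "The proportion of coefficients for each resample that are above zero will indicate the probability that BPT is the most cost-effective option". The section also promises the values of a PANSS improvement at which the likelihood of cost-effectiveness reaches 50%, 75% and 95%.
- **Economic evaluation, delivery:** "Both BPT and Pilates are delivered by a therapist/instructor and in groups so we will be costing both interventions".
- **Statistical analysis:** the outcome models have "fixed effects for the intervention, baseline level of outcome and centre, and random effects for therapy groups". Clustering by therapist or instructor will be examined but not modelled.
- **Proposed sample size:** "Assuming an intra-cluster correlation coefficient for treatment group of 0.1", with inflation factors of 1.6 at end of treatment and 1.45 at six months.

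The Economic evaluation section mentions no therapy group, random effect or group-level resampling. Nor does it say that patients are resampled independently.

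**The concern.** The article treats therapy-group clustering as large enough to model in the outcome analysis and to raise the sample size by 45% to 60%. For costs and net benefit it changes to another method, and the group element drops out without a stated reason. Run as written, a bootstrap regression would most naturally draw single patients with replacement. That treats members of one group as independent.

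The CEAC probability is a share of bootstrap coefficients, so the resampling unit sets it directly. If the bootstrap spread is too small, a probability above 0.5 is reported as too high and one below 0.5 as too low. Net benefit on the PANSS scale contains a PANSS change score. The larger the value placed on a PANSS point, the more that score drives net benefit, and the closer the ICC of net benefit comes to that of the PANSS score. Cost-effectiveness is a declared aim of the trial (Abstract and Discussion), so overstated certainty here would affect a main conclusion.

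**Working it through.** **1. The plan's own figures reproduce.** Inputs from Proposed sample size: difference 3, SD 5, alpha 5% (taken as two-sided), power 90%, ICC 0.1.

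- Unclustered: n = 2 × [5 × (1.960 + 1.282) / 3]² = 58.4 per arm (stated: 58).
- Design effect DE = 1 + (m − 1) × ICC. For m = 7, DE = 1.60 and 58 × 1.6 = 92.8, i.e. 93 as stated. For m = 5.5, DE = 1.45 as stated.
- Six months: 128 × 0.69 = 88.3 and 88 / 16 = 5.5 per group. Power with 88 / 1.45 effective patients per arm is 91.1% (stated: 91%).
- End of treatment: 16 × 7 = 112. Power with 112 / 1.6 = 70 effective patients per arm is 94.4% (stated: 94%).

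The article's clustering arithmetic is therefore sound and can be carried over.

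**2. Which group size applies.** Service use is collected through the six-month follow-up (Outcome measures), so m = 5.5.

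**3. Which ICC applies.** The article gives none for costs, QALYs or net benefit. The 0.1 was set for the PANSS negative scale. I assume a range from 0 to 0.1.

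**4. Effect of resampling patients independently.**

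- Ratio of unclustered to true standard error = 1 / √DE.
- True coverage of a nominal 95% interval = 2Φ(1.96 / √DE) − 1.
- A CEAC value p should be Φ(z_p / √DE), with z = 1.645 for 0.95 and 0.674 for 0.75.

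| ICC (assumed) | DE, m = 5.5 | Interval too narrow by | True coverage | CEAC 0.95 becomes | CEAC 0.75 becomes |
|---|---|---|---|---|---|
| 0 | 1.000 | 0% | 95.0% | 0.950 | 0.750 |
| 0.02 | 1.090 | 4% | 94.0% | 0.942 | 0.741 |
| 0.05 | 1.225 | 10% | 92.3% | 0.931 | 0.729 |
| 0.1 | 1.450 | 17% | 89.6% | 0.914 | 0.712 |

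Worked line for ICC 0.1: √1.45 = 1.204; 1 / 1.204 = 0.830; 1.96 / 1.204 = 1.628, which gives 89.6%; 1.645 / 1.204 = 1.366, and Φ(1.366) = 0.914.

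For p = 0.50, z = 0 and Φ(0) = 0.50 whatever the DE.

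**5. Simulation check.** Setting: 16 groups of 5 or 6 per arm, 2,000 trials, 400 resamples each, percentile intervals, no covariates. Coverage of the patient-level bootstrap:

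| ICC | Normal data | Skewed data |
|---|---|---|
| 0 | 94.2% | 93.5% |
| 0.02 | 93.2% | 92.3% |
| 0.05 | 92.0% | 91.1% |
| 0.1 | 88.3% | 88.2% |

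The decline follows the formula, from a slightly lower start. A simple bootstrap of whole therapy groups covered 92.3% (normal) and 92.6% (skewed) at ICC 0.1. That is better than 88%, but still short of 95% with only 16 groups per arm.

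**The case against.** **The text is silent; it does not exclude clustering.** A bootstrap can draw whole groups, and its regression can carry a random effect. A condensed article may also leave the resampling unit to a full protocol or analysis plan that is not shown. This stands to the extent that the point must be conditional. It does not remove the point. The section already fixes the number of repetitions, the interval types, the CEAC rule, the £5,000 grid and the sensitivity percentages, and the outcome analysis in the same article does name its therapy-group term. A method set out in that detail, with no group element, will most naturally be run without one.

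**The size is unknown.** This stands. Total service costs may have an ICC well below 0.1, and at 0.02 the interval is only 4% too narrow. At £0 per QALY, net benefit is cost alone. The section also refers to PANSS change without naming the negative subscale, so the 0.1 transfers only by analogy.

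**Stronger readings that the article does not support.**

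- *Within-group correlation is built in because staff, training and supervision costs arise per group.* The section speaks of a unit cost for BPT and varies it uniformly. One unit cost applied across an arm adds no variation between groups in that arm. Clustering from this source would need group-specific costing or attendance that clusters by group, and the article states neither.
- *All three reported likelihood values would be wrong.* The 50% value does not move.
- *A reported 0.95 is really about 0.90.* That uses DE 1.6, the end-of-treatment figure. With the six-month DE of 1.45 it is 0.914, and only at ICC 0.1.
- *Therapists should also be resampled.* The Statistical analysis section deliberately leaves therapist clustering out of the analysis. Consistency requires the therapy-group level only.

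**Conclusion.** The point holds in conditional form. The Economic evaluation section specifies its bootstrap regressions without the therapy-group element that the outcome models and the sample size treat as material. A reader might infer that the economic intervals are certain to be too narrow. The article does not show this, because it states neither the resampling unit nor an ICC for any economic outcome.

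Two conditions are needed: independent resampling of patients and a positive ICC. Given both, the direction is fixed. At six months the loss ranges from negligible (ICC 0.02: coverage 94.0%) to material (ICC 0.1: coverage 89.6%, with 0.914 reported as 0.95). These figures rest on 5.5 patients per group, an approximately normal distribution of the estimated difference, and the assumed ICC range. The values to be reported for 75% and 95% likelihood are exposed, and the one for 50% is not. The change is worth making before analysis, since it is cheap and brings the two analyses into line.

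**What to change.** State in the Economic evaluation section that therapy-group clustering is carried into all cost, net-benefit and CEAC analyses, and say how. There are two workable forms:

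1. A net-benefit regression with the same therapy-group random effects as the clinical model. Intervals and CEAC probabilities should then come from that model. Adding a random effect inside a patient-level bootstrap would not be enough, because the spread of the resampled coefficients would still reflect independent patients.
2. A two-stage bootstrap that draws therapy groups within arm and then patients within the drawn groups. It needs shrinkage because there are only 16 groups per arm.

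Either is preferable to a simple bootstrap of whole groups, which covered only about 92% to 93% at ICC 0.1 in the simulation. The two-stage version with shrinkage was not simulated here. Reporting the estimated therapy-group ICC for costs and net benefit would let readers see how much the adjustment mattered.

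The cost is a little more coding, one or two sentences of text, and somewhat wider economic intervals.

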### Proposed sample size

A 20% reduction in the PANSS negative scale has been defined as clinically significant [25], which we would anticipate to be a difference of approximately 3 points given the eligibility criteria. To detect a difference of 3 points, with a standard deviation of 5, at alpha = 5%, and a power of 90%, 58 patients are required in each arm. Assuming an intra-cluster correlation coefficient for treatment group of 0.1, and 7 patients per group with analysable data at the end of treatment gives an inflation factor of 1.6 [24] leading to a required sample size of 93 in each arm. At six months we expect a loss to follow-up of 31%, resulting in 5.5 individuals per group on average and an inflation factor of 1.45; recruiting 128 per arm (16 groups of 8 in each arm) leaves 88 per arm at 6 months and 91% power to detect a difference of 3 points at this time point (see Figure 1). One hundred and twenty eight patients per arm, i.e. 16 groups of approximately 8 patients in each arm will give 94% power for the end of treatment analysis. We do not expect to recruit and allocate exactly eight individuals within each group but the variation in group size will be small and will not materially affect the power of the trial.

**Figure 1 F1:**
[figure not shown]
Flow Diagram.

The estimated loss takes into account drop outs at three different phases of the study, i.e. a) between first interview and beginning of treatment, b) during treatment, and c) during the six months follow up period. Some patients will have to wait up to 5.5 months between giving consent and beginning of treatment. Within that period they could drop out because they change their mind about participation or experience a reduction of negative symptoms so they no longer meet the inclusion criteria. Based on the exploratory trial and clinical experiences in East London, we expect this dropout rate to be less than 10%. During the treatment phase we will have drop outs from treatment in both groups. In line with the intention to treat analysis we will try and follow up all patients who dropped out of treatment in either arm.

In the exploratory trial, the dropout rate from randomisation to 4 month follow-up was 35%. To achieve a lower dropout rate despite a longer follow-up period as compared to the exploratory trial, i.e. 6 instead of 4 month, we will take the following steps:

a) patients will be reimbursed for their expenses and time for each research interview;

b) at each interview (other than the final one at the end of the follow up period), research assistants will already arrange the meeting for the next interview and two weeks before the meeting send a reminder to the patient;

c) the same research assistant will conduct all four interviews with a patient so that a positive relationship can be established;

d) research assistants will work full time on the study so that they are flexible in accommodating the patients’ wishes for meetings at specific times and at specific places including the patients’ homes.

## Discussion

At present there is some limited evidence to suggest that BPT can help reduce the negative symptoms of schizophrenia. This is significant given these particular symptoms are associated with poorer outcomes, and are resistant to most other forms of treatment. The aim of this study is to build on the current evidence base and examine the effectiveness of BPT in a large multi-site trial, examining both the effectiveness and cost-effectiveness in comparison to an active control.

In comparison to the exploratory study which found a strong effect of BPT on negative symptoms [6], the most significant revision, other than the scale of the project, has been to replace the previous control condition of counselling with a structured Pilates group. This modification will allow us to test whether it is the specific components of BPT, i.e. the focus on body experience, the facilitation of emotional group interactions, and the link between movement and emotion, as opposed to the physical activity and the group format which reduces negative symptoms. One possible limitation of using Pilates as a control however is that the non-specific effects of a regular, structured group-intervention, with group facilitator attention and supported attendance as provided in Pilates groups is far from clear.

Implementing the trial design has a number of challenges. By definition, patients experiencing severe negative symptoms have high levels of social withdrawal and low motivation to engage in activities, meaning it might be very difficult to engage participants in study. In addition, the validity of assessing negative symptoms with established measures such as the PANSS has been questioned [26], whilst newer scales developed to address these concerns such as the CAINS [19] have not yet been extensively used.

If the trial does demonstrate the effectiveness and cost-effectiveness of BPT, then this could potentially result in a major development in the treatment of negative symptoms of schizophrenia. Qualified Dance Movement Psychotherapists would require only minimal additional training before they would be able to administer the treatment, and there are also qualified Body Psychotherapists who are able to deliver BPT in groups. Given that the intervention is manualised it can, in theory, be delivered in a consistent and reliable manner. Appropriate spaces as well as the required equipment are likely to be available in most services. Thus, it should be possible to roll out the intervention in the NHS and in mental health services in other countries, and widely offer group BPT to large numbers of patients at limited costs.

In case the trial shows that BPT is effective, this will also be a reason to explore in more depth the potential therapeutic mechanisms involved in the treatment process, such as the linked experience of movement and emotion and the socio-therapeutic facilitation of group interactions through the body oriented interventions. It will also be important to see whether and, if so, to what extent lower negative symptoms translate into improved social contacts and a better quality of life. The latter issue will be addressed in the analysis of secondary outcomes.

## Abbreviations

BPT: Body Psychotherapy; PANSS: Positive and Negative Symptom Scale; NESS: Negative symptoms of schizophrenia BPT trial; NICE: National Institute for Clinical Excellence; DMEC: Data Monitoring and Ethics Committee; TSC: Trial Steering Committee; REC: Research Ethics Committee; CAINS: Clinical Assessment Interview for Negative Symptoms; CSRI: Client Service Receipt Inventory; QALY: Quality Adjusted Life Years; NHS: National Health Service; CEAC: Cost-effectiveness acceptability curve; TAU: Treatment As Usual.
